#### Training

WOD will be delivered by study-employed facilitators with allied health qualifications and training (i.e., psychology, social work, counsellor). Tweddle Child & Family Health Service and the lead investigator will train the health professionals in a 3-day workshop incorporating adult learning principles including: (a) the provision of didactic information (e.g., research into men’s mental health difficulties, theoretical underpinnings of WOD, pilot research findings for WOD); (b) group discussion (e.g., about delivering groups, group process, responding to fathers’ distress and potential safety concerns); and (c) skills practice or behavioural rehearsal of the WOD sessions. Facilitators will be provided with specific training about responding to fathers who may be come distressed, and assessing risk and safety.

### Usual care

WOD will be compared to usual care to evaluate whether it is more effective than care currently received in the community. Fathers allocated to the usual care condition will receive the clinical care typically provided to parents experiencing mental health difficulties by community health and primary health services. A health professional will conduct a brief (~ 30-min) telephone consultation to: (a) enquire about mental health symptoms and conduct a risk assessment for suicidal ideation; (b) provide referral options to telephone support services; and (c) encourage a general practitioner visit to discuss mental health care options. A fidelity checklist will be completed by the health professional to monitor delivery of usual care.

### Follow-up

Fathers will complete online self-report survey measures at 10 and 24 weeks post-randomisation (see Measures below). At 24 weeks post-randomisation, fathers will also complete a researcher-blind mental health diagnostic interview over the telephone (see Measures below). Participant retention strategies will include standardised wording for one email invite and two text and/or telephone reminders to complete surveys.

### Measures

Fathers will be asked to complete online self-report surveys using a web-based data management system at three time points: (i) at baseline (2-4 weeks prior to randomisation); (ii) 10 weeks after randomisation; and (iii) 24 weeks after randomisation. Details of the self-report surveys used to assess the primary and secondary outcomes are presented in Table 2. Fathers will also be asked to participate in a clinical interview for diagnosis of mental health disorders at 24 weeks after randomisation. This interview will be administered via telephone by an appropriately qualified research assistant who is blinded to group allocation.

**Table 2 Tab2:** Study Measures

Outcome	Measure
Primary Outcome	
Mental health difficulties	Kessler Psychological Distress Scale – 10 (K10 [41]): 10 items assessing symptoms of depression and anxiety in last 4 weeks. Widely used in clinical trials for common mental health disorders, with well-established symptomatic and clinical cut-points, high specificity (0.96), and robust total classification accuracy (0.92) to identify mood and anxiety disorders [41].
Secondary Outcomes	
Mental health disorders	The Mini International Neuropsychiatric Interview (MINI): Brief 15-min structured diagnostic interview for common DSM-5 psychiatric disorders, validated for telephone administration and use in clinical trials [42]. Depressive and anxiety disorders will be assessed.
Suicidal ideation	The Suicidal Ideation Attributes Scale (SIDAS [43]): 5-item screener for the presence and severity of suicidal thoughts in the last month based on frequency, controllability, closeness to attempt, level of distress, and impact on daily functioning. Any ideation is indicative of risk for suicidal behaviour; scores > 21 indicate high risk.
Specific mental health symptoms	Depression Anxiety Stress Scale −21 (DASS-21 [44]): 21 items assessing symptoms of depression, anxiety, and stress in the past week, with higher scores indicating greater symptom severity.
Social support	The Medical Outcomes Study-Social Support Survey (MSSS [45]): 14 items assessing perceived availability of tangible, emotional, affective and positive support.
Attitudes to help-seeking	The Barriers to Help Seeking Scale (BHSS [46]): 31 items assessing attitudinal barriers to help seeking for mental health/wellbeing problems.
Unmet need for health services	Adapted Perceived need for Care Questionnaire: Modified version of the Perceived Need for Care Questionnaire [47] asking if different forms of mental health care was need, but could not be accessed.
Parenting self-efficacy	Karitane Parenting Confidence Scale (KPCS [48]): 15 items assessing parents’ perceived parenting self-efficacy or sense of competence in their parenting abilities.
Parent-child relationships	Child-Parent Relationship Scale-Short Form (CPRS): 15 items assessing parents’ perceptions of their relationship with their child [49].
Stressful life events	Adapted Pregnancy Risk Assessment Monitoring System (PRAMS [50]): 25 items asking about stressful life events experienced in the last year.
Health economic outcomes	
Quality of life	The Assessment of Quality of Life 8 dimension (AQoL-8D [51]) is a validated tool assessing quality of life impacts in economic evaluation. The AQoL-8D is particularly suited to measuring mental health aspects of quality of life.
Health service use and health care costs	Study designed self-reported type, number and cost of healthcare services accessed, and examination of linked MBS/PBS data covering 24 weeks from baseline to follow-up.

### Process evaluation

The objectives of the process evaluation are to generate evidence about how to: (a) guide refinement of the WOD intervention, training and resources, (b) inform decisions that health services need to make to adopt WOD, (c) support high quality implementation of WOD, and (d) enable sustained use and wider deployment of WOD in the future. This evaluation will be guided by the RE-AIM model [38] and the EPIS framework [39]. This approach will identify the intervention elements and eco-system (e.g., health service setting factors; policy context, policymakers) likely to influence the reach, adoption, implementation, scalability and population impact of WOD. Sources of data for the process evaluation include recruitment campaign monitoring, screening and eligibility information, participant tracking information, reflections from the study team, health services and father advisory group, and qualitative interviews with fathers who participate in WOD and usual care.

### COVID-19 pandemic safety measures and contingency planning

State government and institutional COVID-19 safety procedures and public health regulations will be adhered to at all times. This includes: (a) having current COVID-19 safety plans in place for all research and community locations (office, WOD group, active face-to-face recruitment sites), and (b) participant screening for COVID-19 symptoms, temperature testing upon arrival, maintaining physical distancing requirements, cleaning and hygiene procedures, minimising equipment sharing, and use of personal protective equipment where required. All research staff and WOD facilitators will undertake training in COVID-19 safety procedures. Any suspected or confirmed cases of COVID-19 will be reported via the sponsoring institution (Murdoch Children’s Research Institute; MCRI) incident reporting portal.

Whilst WOD has been designed for face-to-face in-person delivery, the program can be delivered via a telehealth platform in the event of a government public health directive to cease face-to-face gatherings. All fathers will be posted or emailed the required resources prior to the session/s (e.g., session handouts and materials). WOD will be delivered as intended, and the fidelity checklist will be completed by the WOD facilitator. The facilitator will be required to reflect upon and provide brief notes on the process issues of delivering online (e.g., challenges to delivering content or facilitating activities including the personal training component, quality of the interactions between fathers, level of participation by fathers). If face-to-face delivery is permitted, any remaining WOD sessions will resume face-to-face at the booked venue in the local community.

With respect to the COVID-19 pandemic and other extenuating circumstances leading to unplanned methodological, ethical and analytical challenges and changes, we will submit any protocol modifications for approval and update the trial registry. We will use the the CONSERVE (CONSORT and SPIRIT Extension for RCTs Revised in Extenuating Circumstances) statement to ensure transparency and completeness of reporting of any modifications [52].

### Risk and safety management

Risks can include: (a) risks to the safety and rights of the study participants; (b) risks to the successful conduct of the study; and (c) risk to the wellbeing of WOD facilitators and research staff undertaking recruitment and data collection. A trial-specific risk and safety assessment and response plan has been conducted by the Trial Steering Committee. In brief, the Principal Investigator will be notified of any safety or adverse concerns to assess severity, seriousness, and likelihood of the event to the trial conditions. These will be discussed at the Trial Steering Committee or the HREC as soon as possible to determine action (e.g., withdrawal, referral).

A comprehensive plan to minimise and respond to any psychological distress or safety issues for the study participants has been approved by HREC. This includes but is not limited to: (a) clear information in the Participant Information and Consent Form about why the study is being conducted, what it will involve, the potential risks and burdens of participation, and the opportunity to opt out of the study at any time; (b) follow-up and psychological risk assessment for any participants who score at the clinical cut points on the mental health and suicide assessment measures; (c) responding to distress in WOD or Usual Care conditions; and (d) monitoring and responding to distress or inappropriate exchanges on the WhatsApp group.

To maintain wellbeing of research staff and facilitators, training in responding to participant distress (as described above), comprehensive fieldwork guidelines, and regular supervision will be provided by the lead investigator who is a trained psychologist. Regular group supervision will also provide opportunities to process concerns in responding to participant distress or safety concerns, as well as monitoring staff wellbeing.

### Data management

All study data will be collected and managed using a secure web platform, online electronic data capture tools, hosted at MCRI. All personal and identifying information will be kept separate from trial data and linked by an ID. All data will be password protected and on secure platform at MCRI. Data will only be accessible by the research team.

### Data analysis

Primary analyses will follow the ‘intention to treat’ (ITT) principle at the level of the individual participant. In the ITT analysis participants are compared according to the group to which they were randomly allocated, regardless of participants’ compliance or withdrawal from the trial. Analysis of the primary outcome and all secondary outcomes will be done using generalised linear mixed effects models, with WOD group assigned as a random effect. The geographic location stratification variable, LGA, will be included in the model. For the primary analysis, the model based mean K10 score in each trial arm will be compared at 10 weeks and at the 6-month follow-up (primary outcome). Model-based effect estimates will be reported along with 95% confidence intervals. Binary endpoints will be analysed using generalised estimating equations, with WOD group as random effect and stratified by LGA. No interim analyses will be conducted.

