**Methods:**

This trial will employ a parallel-arm randomised controlled trial (RCT) to evaluate the effectiveness and cost effectiveness of WOD peer support group intervention compared to usual care (a 30-min mental health and service focused phone consultation with a health professional). A total of 280 fathers of young children (aged 0-4 years) who are experiencing mental health difficulties and/or are at risk of poor mental health will be recruited.

Randomisation and analyses will be at the level of the individual participant. The primary outcome is psychological distress symptoms, measured by the Kessler Psychological Distress Scale (K10) from baseline to 24 weeks post randomisation. A range of secondary outcomes will be assessed including suicidal ideation; mental health disorders, specific symptoms of depression, anxiety, and stress; social support, quality of life, health service use, and health care costs. Data will be collected at baseline, 10- and 24 weeks post-randomisation.

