### Screening & inclusion/exclusion criteria

Once consent is obtained, fathers will be directed to complete the online screening survey. To be included in the trial, fathers need to meet the following criteria:Be a father (biological, step-, or other male caregiver) of a child age 0-4 years, and in regular weekly contact with the childHave mental health difficulties above the symptomatic cut-point on the Kessler Psychological Distress Scale-10 item (K10; i.e., a score of > 20, see Measures below for detail); *and/or* have at least two risk factors for trajectories of increasing mental health difficulties among men across early fatherhood [40], including: a) history or mental health difficulties; b) relationship difficulties; c) high work-related stress; d) unemployment; or e) have a child with sleep difficulties, a disability, chronic illness, or other special health care needBe aged 18 years or olderHave sufficient English fluency to complete surveys and participate in the intervention.

Fathers will be ineligible to participate in the trial if they: a) have a severe mental health disorder (i.e., self-reported psychosis, substance use dependency) that may require more intensive mental health treatment; b) have an overt indicator of family violence (e.g., self-reported intervention order or court case for family violence); or c) have child protection service involvement. Following screening, the research team will contact fathers to confirm ineligibility and provide general information about mental health support available in the community (i.e., family doctor, online resources, telephone helplines).

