### Sample size

A sample size of 14 peer groups per study arm with 9 individuals per group has 80% power to detect a difference of 0.4 (Cohen’s d) between standardised K10 group mean scores when the intracluster correlation (ICC) is 0.02 using a 2-sided t-test at the 0.05 significance level. The number of participants per group was increased to 10 to allow for loss to follow-up of ~ 10%. This requires recruitment of 140 participants per treatment arm.

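### The stated primary model names LGA but not baseline K10; planned power is still met, but precision available at no cost is forgone

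*Protocol article*

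**What the plan says.** The Data analysis section gives the model family (generalised linear mixed effects), the random effect (WOD group) and the contrast (model-based mean K10 by arm at 10 weeks and at 6 months, the latter being primary). On covariates it says: "The geographic location stratification variable, LGA, will be included in the model". It names no other fixed covariate, and it does not mention baseline K10 either as a covariate or as a repeated outcome.

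Baseline K10 is available for every randomised father:

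- One route to eligibility is a score "above the symptomatic cut-point on the Kessler Psychological Distress Scale-10 item (K10; i.e., a score of > 20"), so the K10 is already taken at screening (Screening & inclusion/exclusion criteria).
- The self-report surveys are scheduled at baseline, 10 weeks and 24 weeks (Measures).
- Allocation is revealed only after the baseline questionnaire is complete (Randomisation).

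The sample size was set without any credit for baseline adjustment. The Sample size section reports that "A sample size of 14 peer groups per study arm with 9 individuals per group has 80% power". Its basis is a plain two-sided t-test at 5%, with an ICC of 0.02 and a target standardised difference of 0.4.

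The abstract describes the primary outcome as distress "measured by the Kessler Psychological Distress Scale (K10) from baseline to 24 weeks post randomisation". Aims and hypotheses states it as lower distress at 24 weeks.

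**The concern.** The pre-randomisation value of a symptom score usually carries information about its later value, and a model that uses it estimates the treatment effect more precisely. Two features of this trial make that relevant. Fathers can enter on a raised K10, on two risk factors, or on both, so symptomatic and at-risk-only fathers are mixed. Randomisation is stratified by LGA alone, so balance on baseline K10 is left to chance.

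At stake is the width of the confidence interval for the primary result, and with it the chance of detecting the target difference. Validity is not at stake. The abstract's wording adds a smaller difficulty: it refers to baseline, but the analysis text does not turn that reference into a model term.

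**Working it through.** **Inputs from the Sample size section.** 14 groups per arm, 9 analysed per group (126 per arm), d = 0.4 with SD 1, ICC 0.02, two-sided alpha 0.05, t-test. Raising the group size from 9 to 10 for about 10% loss gives 14 × 10 = 140 per arm, which agrees with 126/0.9 = 140.

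**Step 1: reproduce the stated power.**
- Design effect: 1 + (9 − 1) × 0.02 = 1.16.
- Effective n per arm: 126/1.16 = 108.6.
- Variance of the difference: 2 × 1.16/126 = 0.01841; standard error 0.1357.
- Noncentrality: 0.4/0.1357 = 2.948.
- Degrees of freedom for a t-test on clusters: 2 × 14 − 2 = 26; critical value 2.056.
- Power from the noncentral t: **81.0%**.

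With 13 groups per arm the same calculation gives 77.8%, so 14 is the smallest number of groups that reaches 80%. The plan's figure is reproduced.

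**Step 2: add baseline K10.** Let r be the correlation between baseline and 24-week K10. The article gives no value, so r is an assumption and is shown over a range. If adjustment shrinks the whole outcome variance, the variance of the difference becomes 0.01841 × (1 − r²). At r = 0.5 this is 0.01841 × 0.75 = 0.01381, the noncentrality is 0.4/√0.01381 = 3.404, and power is 90.6%.

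A more cautious version leaves the between-group variance (0.02) untouched and shrinks only the within-group part. The variance of the difference is then 2 × [0.02 + (0.98 − r²)/9]/14.

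| Assumed r | Whole variance shrinks | Gain over 81.0% | Only within-group variance shrinks | Gain over 81.0% |
|---|---|---|---|---|
| 0.3 | 84.5% | 3.5 points | 84.0% | 3.0 points |
| 0.4 | 87.2% | 6.2 points | 86.3% | 5.3 points |
| 0.5 | 90.6% | 9.6 points | 89.3% | 8.3 points |
| 0.6 | 94.4% | 13.4 points | 92.7% | 11.7 points |
| 0.7 | 97.8% | 16.8 points | 96.2% | 15.2 points |

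**Step 3: sensitivity to where the clustering sits.** The planned model has a random effect for WOD group, and usual care is a single telephone consultation. If only the WOD arm is clustered, the variance of the difference is (1.16 + 1)/126 = 0.01714. With 26 degrees of freedom, power is 83.7% unadjusted and, with the whole variance shrinking, 86.9%, 92.4% and 98.4% at r = 0.3, 0.5 and 0.7. The gains are 3.3, 8.8 and 14.8 points.

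Across these versions the gain is about 3 to 17 points, and its size depends mainly on r.

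**The case against.** The strongest objection is that this is a condensed journal article. It says LGA will be in the model; it does not say that LGA is the only covariate. The full protocol or SAP, neither of which is shown, may add baseline K10. A longitudinal model with baseline as a repeated outcome would also fit the three survey times and the abstract's wording. This stands to the following extent: a reader might infer that the primary analysis adjusts for LGA alone, and the article does not establish that. It does, however, state the model family, random effect, covariate and contrast, and baseline K10 is absent from that statement.

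Three other stronger readings are tempting and are not supported.

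- **That the trial is underpowered, or loses about 10 points of planned power.** The sample size took no credit for baseline adjustment, and 80% is met without it. A figure near 10 points belongs to r of about 0.5, which is not in the article.
- **That it is unknown whether change or final score is tested.** Aims and hypotheses and Data analysis both point to the 24-week score. One loose phrase in the abstract does not override them, though it should be aligned.
- **That chance imbalance in baseline K10 would bias the result.** Under randomisation the unadjusted estimate is unbiased, and its confidence interval already allows for chance imbalance. Adjustment removes avoidable noise; it does not repair a bias.

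**Conclusion.** The point holds as a recommendation on precision. The stated primary model names LGA and a WOD-group random effect but not the baseline value of the primary outcome, which is in hand for every father before allocation. Planned power is intact at 81.0%. Naming baseline K10 would raise power at the same sample size to about 84% to 98% for r between 0.3 and 0.7. Those figures rest on the plan's own d, ICC, group size and number of groups, on 26 degrees of freedom, on a linear relation between baseline and follow-up K10, and on an assumed r. If an unseen SAP already includes baseline K10, the point reduces to aligning the article's text.

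**What to change.** - In Data analysis, add baseline K10 to the primary model as a continuous covariate alongside LGA. Alternatively, model baseline as a repeated outcome with the arm means constrained equal at baseline.
- Do the same for each secondary outcome that is measured at baseline, using its own baseline value.
- State the primary estimand as the adjusted mean difference in K10 at 24 weeks, and align the abstract's phrase with it.
- If the full protocol or SAP already adjusts for baseline K10, make the article's description match.

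An arm-by-baseline interaction may be reported if the investigators want it, but it is optional and not part of this correction. The cost is a sentence or two of text, with no new data and no change to the sample size. The change should be fixed before outcome data are examined by arm.

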### Health economics analysis

Costs of administering WOD (staff time to run groups based on number and duration of groups, training, materials, supervision, gym, travel) will be estimated drawing on the study protocol, administrative records and budgets. Analysis of costs will also include costs associated with the treatment of depression and anxiety from linked administrative data providing information on mental health care visits and prescriptions and from self-report of healthcare use. Quality of life between groups will be compared using AQoL-8D scores at baseline and 6-month follow-up. Self-reported impacts of poor mental health on employment and lost time from work will also be analysed to assess productivity impacts. The incremental cost-effectiveness ratio at the 6-month follow-up period will be calculated in terms of cost per quality-adjusted life year (QALY) and cost per primary outcome (K10) change. If there are significant differences in outcomes between control and treatment groups at follow-up, a decision analytic model will be used to extend the analysis to long-term impacts by modelling cost-effectiveness drawing on existing depression long-term simulation models. We will estimate the public healthcare budget impact of WOD under different scales of roll-out, including roll-out in Early Parenting Centres in Victoria and potentially Australia. Costs and outcomes will be discounted at 5%, and sensitivity analyses will be performed to determine the impact of changes to key parameters. The model will be extended to take into account the distribution of costs and benefits across the population to determine the impact of the intervention on equity.

